## STATISTICAL ANALYSIS PLAN

$\Delta = (\text{measure at 18 months} - \text{measure at inclusion})$

The four comparisons will be first conducted according to the intent to treat principle with “missing = failure” strategy (see §2.3 for comparative statistical tests) for handling missing data on primary endpoints. A failure is defined as the minimum change between baseline and 18 months observed in the whole population study. This first analysis will be the main result of the study.

This first analysis will be complemented with a sensitivity analysis to check the robustness of the main analysis to missing data. The maximum bias strategy for missing data will be performed. Missing data will be replaced by a failure of the strategy in one group and by a success of the strategy in the other, and vice versa. The success is defined as the maximum change between baseline and 18 months observed in the whole population study. The failure is defined as the minimum change between baseline and 18 months observed in the whole population study.

We will be able to conclude that the first analysis is robust if all sensitivity analyses have a similar conclusion.

The main and sensitivity comparative analyses will be performed with adjustment on baseline prognostic factors (age, education, gender, MMSE) (see §2.3 for statistical models).

A per-protocol analysis will be performed, using the strategy defined in §2.1.1.

An analysis of the effect of the exposure to meditation (number of hours of practice, number of sessions...) will be performed using the strategy described in §2.3.

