### 11.2. *Calculation of the study size*

#### Study on non-expert seniors:

The comparison between the meditation group and the no-intervention group is going to focus on the difference in 1) volume and 2) perfusion of the anterior cingulate cortex 18 months after the start of the intervention compared to the value at inclusion, with an expected effect size of 0.75 (effect size of short-term meditation vs. no intervention, from a meta-analysis on the effects of meditation on brain imaging markers: Fox et al, 2014). Given that the intervention in the current protocol is 18 months, we consider that the effect size will be at least equal to 0.75.

The same effect size of 0.75 is expected for the comparison between the meditation group and the English learning group on the difference in 1) insula volume and 2) insula perfusion 18 months after the start of the intervention compared with the inclusion value.

To show an effect size of 0.75 for each comparison, with 80% power and a two-sided first-species risk of 1.25% (Bonferroni correction because four comparisons will be performed) 42 participants per group must be recruited for a total of 126 participants.

Assuming that the effect size assumptions are conservative and that precautions are taken at the time of recruitment to best ensure adherence of participants to the trial, we expect that the risk of dropout after knowledge of the randomization group is very low and that the power of the study is preserved. However, we will implement close monitoring of these refusals at the beginning of the trial. In order to increase the statistical power of the secondary analysis on the FDG-PET examination carried out from

the second wave of inclusion, 24 participants will be recruited in addition, i.e. 8 additional participants per group (meditation, English, passive control) for a total of 150 participants.

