#### **11.3.1. Analysis strategy**

The main analysis will be carried out on an intention-to-treat basis, i.e. all randomized patients will be included in the analysis in the group in which they were initially randomized, and all their data will be used regardless of their changes in strategy during the research, with the "missing = failure" strategy, i.e. any missing value will be replaced in the analysis by the value corresponding to failure (minimum difference between 18 months after the intervention and inclusion), estimated on the data observed in all groups combined.

In order to assess the robustness of the results, a sensitivity analysis to missing data will be performed using the maximum bias strategy by using the values reflecting the failure and success (minimum and maximum difference respectively) estimated on the observed data for all groups combined.

A sensitivity analysis will also be performed by including only participants who attended at least 20% of the meditation sessions and exercises and who completed the examinations for the primary judgement criterion.

Some features may be strongly associated with volume and perfusion of the anterior cingulate cortex or insula. These characteristics could play a confounding role if, despite randomization, an imbalance was observed. Therefore, the comparative analysis of the primary judgemental criteria could be adjusted for potential confounders such as age, education, and gender. These adjustments may require the use of appropriate models, the relevance of which will be discussed according to the distribution and type of variables.

The description will always be done globally and by treatment group.

Tests for the primary criteria will be performed at the risk of error of the first kind  $\alpha = 1.25\%$ .

Tests for secondary criteria will be performed at the overall risk of error of the first kind  $\alpha = 5\%$ .

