### **11.3.5. Analysis of the main criteria**

The comparison between the meditation group and the foreign language learning group will look at the difference in 1) volume and 2) perfusion of the anterior cingulate cortex 18 months after the start of the intervention compared to the value at inclusion.

The comparison between the meditation group and the no-intervention group will look at the difference in 1) insula volume and 2) insula perfusion 18 months after the start of the intervention compared to the value at baseline.

The main criteria will be compared between groups by Student's t test or Wilcoxon test if the hypothesis of normality of the criteria is not verified.

An analysis of the effect of the level of exposure to meditation (number of hours of practice, number of sessions, etc.) will be performed by including all participants.

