### **For the randomized clinical trial with non-expert seniors:**

The comparison of the meditation vs. no intervention arms will focus on the change in 1) volume and 2) metabolism of the anterior cingulate cortex from baseline to the end of the 18-months intervention, with an expected effect size of 0.75.

We expect the same effect size of 0.75 for the comparison between the meditation arm and learning of English arm on the change in 1) volume and 2) metabolism of the insula from baseline to the end of the 18-months intervention.

To demonstrate an effect size of 0.75 for each of the four comparisons, with 80% power and a two-sided type I error of 1.25% (Bonferroni correction for test multiplicity), 42 participants per arm need to be included for a total of 126 participants.

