#### 2.1.3 Type I error rate

The statistical tests for the main objectives (1 + 1bis) will be performed with 1.25% error rate each, controlling the family-wise error rate to 5% for the 4 comparisons.

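### The primary analysis is valid, but it leaves out the region's own baseline value as a covariate and uses single-step Bonferroni, so it gives away a modest amount of power.

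*Combined protocol and SAP*

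**What the plan says.** SAP 3.6.1 defines each endpoint as the 18-month value minus the inclusion value. It runs the four comparisons by intention to treat, replaces missing outcomes with the smallest observed change, and names that first analysis as the study's main result. It then adds: "The main and sensitivity comparative analyses will be performed with adjustment on baseline prognostic factors (age, education, gender, MMSE").

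Protocol 11.3.5 says of the primary endpoints that they "will be compared between groups by Student's t test or Wilcoxon test if the hypothesis of normality of the criteria is not verified". SAP 2.3 adds a t test for unequal variances, and linear regression for adjustment where needed. Protocol 11.3.1 makes adjustment optional and ties it to an observed imbalance: the comparison "could be adjusted for potential confounders such as age, education, and gender".

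On multiplicity, SAP 2.1.3 has the tests "performed with 1.25% error rate each, controlling the family-wise error rate to 5% for the 4 comparisons". Protocol 11.2 sizes the trial on the same basis: "To show an effect size of 0.75 for each comparison, with 80% power and a two-sided first-species risk of 1.25"%. That gives 42 per arm, later raised to 50 per arm to help the FDG-PET analysis.

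Protocol 6.6 schedules MRI and Amyvid PET for all participants at V1. Protocol 6.7 places randomization after the V1 examinations of the whole wave are complete.

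**The concern.** A change score uses the baseline by subtraction, which fixes its slope at 1. ANCOVA estimates that slope. For any baseline/18-month correlation below 1 it therefore has smaller residual variance, and it removes the effect of a chance baseline imbalance. The value is measured before allocation, so it is a legitimate covariate. The plan adjusts for four other baseline variables and not for this one.

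Section 2 of the protocol frames the hypotheses as volume and/or perfusion, so each of the four tests carries its own claim. Holm rejects everything that single-step Bonferroni rejects, and sometimes more, at the same 5% family-wise error under any dependence between the tests.

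Wording is also at stake. The SAP says adjustment will be done, while the protocol says it could be done if groups look unbalanced. The two should give one rule.

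**Working it through.** **Inputs from the documents.** Standardised effect 0.75; two-sided 1.25% per test, four tests; 80% power; 42 per arm stated, 50 per arm planned; 1:1:1 allocation.

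**Inputs assumed.** Baseline/18-month correlation r from 0.8 to 0.98; equal variance at both visits; correlation between the four outcomes 0, 0.3 or 0.6. The documents give none of these.

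**Step 1: the plan's own figure.** With the noncentral t, noncentrality is d × √(n/2). At n = 42 this is 0.75 × √21 = 3.44, and power is 80.9%. At n = 41 power is 79.7%, so 42 per arm is exactly right. At n = 50, noncentrality is 0.75 × √25 = 3.75 and power is 88.3%. The error budget is 4 × 1.25% = 5%.

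**Step 2: adding the baseline covariate.** Var(change) = 2σ²(1 − r). The ANCOVA residual variance is σ²(1 − r²). The ratio is (1 + r)/2, so the effective effect size is 0.75/√((1 + r)/2). Power per test at 1.25%:

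- No baseline covariate: 80.9% at 42 per arm, 88.3% at 50.
- r = 0.8: ratio 0.90, effective d 0.791; 85.4% and 91.8%.
- r = 0.9: ratio 0.95, effective d 0.769; 83.2% and 90.1%.
- r = 0.95: ratio 0.975, effective d 0.760; 82.0% and 89.2%.
- r = 0.98: ratio 0.99, effective d 0.754; 81.3% and 88.7%.

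The share of change-score variance that baseline explains is (1 − r)/2: 10% at r = 0.8, 5% at 0.9 and 1% at 0.98. The lost degree of freedom costs less than 0.1 point.

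These are complete-data figures. Replacing missing outcomes with the minimum observed change weakens the link between baseline and change, so the gain shrinks as missing data increase.

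**Step 3: Holm.** Ordered p-values are compared with 5%/4 = 1.25%, 5%/3 = 1.67%, 5%/2 = 2.5% and 5%. Four t tests with a shared meditation arm were simulated (20,000 to 40,000 trials per setting), without the baseline covariate, at 42 per arm:

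- One real effect: 81% under both rules.
- Two real effects of 0.75: about 81% to 83% per test.
- Four real effects of 0.75: about 81% to 89-90% per test.
- At least one rejection: identical under both rules in every setting, because Holm's first step is Bonferroni.
- No real effect: family-wise error 4.5% to 5.0%, identical under both rules.

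**The case against.** The strongest reply is that nothing here is wrong. The tests are valid under randomization, family-wise error is held at 5%, the sample size reproduces, and single-step Bonferroni with matching intervals is a legitimate choice. All of that stands.

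A reader might infer more than the documents support:

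- *That the baseline value is the strongest predictor of change.* No section says so. If r for regional volume is near 0.98, baseline explains about 1% of the change, and the ANCOVA argument is almost empty for two of the four endpoints.
- *That either the adjusted or the unadjusted test can be declared the result.* SAP 3.6.1 names the first intention-to-treat analysis as the main result, and its t, Welch or Wilcoxon rule is set in advance. What remains is narrower: the later sentence about adjustment, and the protocol's imbalance condition, do not settle whether the headline p-value is adjusted.
- *That the trial starts from 81% power.* That is the figure at 42 per arm. At the planned 50 it is 88%.
- *That Holm makes the trial more likely to succeed.* On an and/or reading, one rejection is enough, and that probability does not move.

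The objection on cost also stands. The 1.25% level, the t test/Wilcoxon rule and the conditional adjustment are protocol text as well as SAP text. Timing matters too: protocol 10.5 has the frozen database through V3 handed over after 31 December 2020, while the current protocol is dated 07/01/2022.

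**Conclusion.** The point holds as an efficiency improvement with one wording conflict to resolve. At 50 per arm and an effect of 0.75, the baseline covariate is worth about 3.5 points of power at r = 0.8, about 2 at r = 0.9, and under 1 at r = 0.95 to 0.98, less whatever minimum-value imputation removes. Holm is worth about 2 points per test with two real effects and 8 to 9 with four (at 42 per arm), and nothing with one. All of this rests on assumed correlations, equal variances at the two visits, and a true effect of 0.75. It does not cast doubt on the validity of the planned result.

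**What to change.** 1. Name one primary model: ANCOVA of the 18-month change on arm, baseline value of the same regional measure, age, gender, education and MMSE. Keep the unadjusted t test or Wilcoxon as supportive.
2. Delete the imbalance condition in protocol 11.3.1, so that it agrees with SAP 3.6.1.
3. Replace the fixed 1.25% per test with Holm at family-wise 5%. Leave the sample size unchanged.

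**Cost.** No new data. Matching edits are needed in the protocol (synopsis, 11.2, 11.3.1, 11.3.5) and the SAP (2.1.3, 3.6.1), with the protocol's substantial-amendment procedure (16.1) if it applies. One degree of freedom is spent. Simultaneous intervals are less simple under Holm, so report unadjusted 95% and Bonferroni 98.75% intervals side by side.

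**Timing.** The change must precede database freeze and analysis, as the SAP's purpose statement requires for its own approval. If that point has passed, keep the planned analysis as primary and report ANCOVA and Holm as labelled supportive analyses.

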## Acronyms

---

|               |                                           |
|---------------|-------------------------------------------|
| CI     | Confidence Interval                       |
| EUCLID | EUropean CLInical trials & Development    |
| ICH    | International Conference on Harmonisation |
| WP     | Work Package                              |

## PURPOSE

---

This document describes the steps and methods of the statistical analysis to implement in order to answer the research question of the study expressed by the secondary objectives (objectives 2 to 9) of the protocol. This document must be approved by the trial steering committee (TSC) prior to any analysis and database freezing.

## Trial summary

---

This document is based on protocol v9.0 of 08 July 2020 and protocol v10.0 of 10 December 2020.

### Context

As the number of older people in Europe grows, increasing healthy life years is a priority. As we live longer, ensuring good mental as well as physical health into later years is becoming ever more important. Cognitive decline, dementia (e.g. Alzheimer's disease, AD), sleep disturbances and depression, all related to psychological distress and anxiety, are significant drivers of reduced quality of life (QoL) in older adults. This project builds on evidence that meditation practice have the potential to downregulate these adverse factors and positively affects mental and neurological conditions including AD.

### Trial objectives

#### Main objectives

OBJECTIVE 1: To compare the effect of an 18-month mindfulness-based intervention versus no intervention on volume and perfusion of anterior cingulate cortex, in healthy older adults.

OBJECTIVE 1BIS: To compare the effect of an 18-month mindfulness-based intervention versus an 18-month intervention based on language learning, on volume and perfusion of insula, in healthy older adults.

#### Secondary objectives

○ In relation to the interventions studied:

OBJECTIVE 2: To compare the effect of an 18-month mindfulness-based intervention, an 18-month intervention based on language learning and no intervention, on areas of cognition, psycho-affective/emotion, compassion, support, mindfulness, sleep, wellbeing, quality of life, and on biological and radiological measures, including sex-specific effects;

OBJECTIVE 2bis: To estimate the maintenance of the effects of the interventions (mindfulness-based training and language learning) 29 mois +/- 6 mois months after the end of the intervention on areas of cognition, psycho-affective/emotion, compassion, support, mindfulness, sleep, wellbeing, quality of life (and on biological and radiological measures depending on budget availability);

OBJECTIVE 2ter: To compare the long-term effects (29 mois +/- 6 mois months after the end of the intervention) of the two interventions (the 18-month mindfulness-based intervention and the 18-month intervention based on language learning) on areas of cognition, psycho-affective/emotion, compassion, support, mindfulness, sleep, wellbeing, quality of life (and on biological and radiological measures depending on budget availability);

OBJECTIVE 3: To compare the effect of an 18-month mindfulness-based intervention and of an 18-month intervention based on language learning vs. no intervention on participants' partners (perception of participant's changes, interactions with the participant, willingness to help the participant).

OBJECTIVE 3bis: To estimate the effects of the interventions (meditation and foreign language learning) on participants' partners (perception of participant's changes, interactions with the participant, willingness to help the participant) 21 months after the end of the intervention.

OBJECTIVE 3TER: To estimate the effects of the interventions (meditation and foreign language learning, during 18 months) (acceptance of the interventions, perception of changes...).

○ Without relation to the interventions studied:

OBJECTIVE 4: To estimate the association between meditation practice and behavioral and biological measures (cognition, psycho-affective, lifestyle, blood, sleep and radiological measures), by comparing expert meditators and participants with no previous meditation practice;

OBJECTIVE 5: To identify neural signatures of mindfulness and compassion meditations in senior expert meditators;

OBJECTIVE 6: To estimate the association between lifestyle factors (cognitive activities, diet, physical activity), and psycho-affective, behavioral, and biological measures, including sex-specific or sex-mediated associations;

**OBJECTIVE 7:** To explore pathophysiological processes underlying Alzheimer's disease, by studying associations between several measures, and the association between structural and functional connectivity and lesion propagation, including sex-specific associations (link with data collected in the IMAP+ study).

**OBJECTIVE 8:** To compare PET-FDG measurement to early PET-Amyvid® perfusion measurement to better understand the links (and possible modifications of coupling) between metabolism and perfusion and compare the sensitivity of the two measures to evaluate the effects of the 2 interventions;

**OBJECTIVE 9:** To identify the determinants of well-being and mental health in ageing on participants of the passive condition (control group) and participant' partners on areas of cognition, psycho-affective/emotion, compassion, support, mindfulness, sleep, wellbeing, quality of life (and on biological and radiological measures depending on budget availability).

## **Trial design**

- Randomized, controlled, observer-blinded monocentric, superiority trial, with three parallel groups (an 18-month mindfulness-based intervention, an 18-month intervention based on language learning and no intervention), on healthy older adults aged 65 years and more and with no previous meditation practice.
- Cross-sectional observational study, aiming to estimate the association of meditation practice with health markers, by recruiting senior expert meditators and comparing them with participants without previous meditation practice.

## **Interventions studied**

For both the mindfulness-based intervention and the intervention based on language learning, participants will follow:

- 2-hour weekly group sessions,
- Daily home practice (at least 20 minutes per day),
- Some days or half-days of more intense practice.

Each weekly group session will be divided into three parts: presentation, sharing, and practice. Participants will be strongly encouraged to participate in all those activities during the whole period of intervention (i.e. 18 months).

### **Meditation arm:**

The intervention in the meditation arm will be provided by expert meditator instructors at the "Pôle de formations et de recherche en santé (PFRS)", in Caen. This intervention will consist in a secular programme of meditation training proposed in an objective of personal development and healthy ageing. This 18-month intervention programme is designed for individuals aged 65 years or older, retired, in good general health and leaving at home. The objective of this intervention programme is to develop mindfulness and compassion abilities as additional psychological resources to cope with challenges related with ageing on physical, cognitive and psychological aspects.

### **Language learning arm:**

The intervention in the language (English) learning arm will be performed by teachers from the Carré International, a department from Caen University specialized in foreign language teaching and experienced in teaching to seniors. This intervention will consist in English exercises designed to reinforce each participant's abilities in understanding, writing and speaking.

### **No intervention arm:**

No intervention will be delivered to participants assigned to this arm, during the study duration.

## **Randomization**

The randomization list will be generated centrally by the biostatistician at the EUCLID clinical trials platform prior to the start of the study and kept confidentially in a secure environment. The sample size of each randomized group will be balanced with a ratio of about 1:1:1.

- Group 1: Meditation

- Group 2: Learning of English (active control)
- Group 3: No intervention

A working sheet presenting the entire randomization process will be kept confidentially at the EUCLID clinical trials platform

## Eligibility criteria

### Inclusion criteria

#### For all participants

- Age  $\geq$  65 years;
- To be autonomous (assessed with the following question asked by the clinician: “would you be able to live alone (from a functional (not affective) point of view »?);
- Live in their home;
- Educational level  $\geq$  7 years (from the Preparatory Course (First grade) included);
- To be registered to the social security system;
- To be motivated to effectively participate in the project and to sign the consent form in agreement with the local ethic committee (Comité de Protection des Personnes);
- Neuropsychological performances within the normal range (according to age, sex, and educational level), as assessed by the diagnostic battery.

